Drawing on previous research and theories on social networks and translation of information contagion into attitudes and behaviors, several network characteristics which may influence the delivery of primary care for CVRM by health professionals and self management of patients at risk for CVD and with established CVD can be inferred. For a schematic representation of the hypothesized relations see Figure 1. For healthcare professionals we expect a number of social network characteristics to be of importance. Firstly, a high density (the proportion of all possible connections in a given network that are actually present) is expected to be beneficial as it provides multiple opportunities for various social influence mechanisms, such as for example imitation of successful behaviors and social comparison [8,16,17]. Secondly, a high frequency of contacts (within existing relationships) is expected to be important, as this enhances social influence and offers protection against egocentric choices [16,18,19]. Thirdly, high homogeneity of individuals in a network (e.g. regarding educational background) is expected to enhance social comparison uptake of information items that are disseminated in the network [20]. Fourthly, individuals with high centrality in a social network are expected to be influential as they have many connections and high centrality has been associated with enhanced knowledge transfer [21,22]. In healthcare, individuals with high centrality are expected to be present in social networks as CVRM-coordinators or case managers. Both are purposefully created to become highly central individuals in healthcare delivery networks. Fifth, an informal opinion leader may be identifiable in a network. He or she represents a person who influences opinions, attitudes, beliefs, motivations, and behaviors of others [23]. For these network-related factors, it may be noted that the direction of the social influence (e.g. better or worse CVRM) depends on the content of the information that is shared.

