#### Hypotheses on health professionals

Patients are more likely to receive recommended CVRM and reach CVRM targets in general practices which have social networks characterized by: high density, high frequency of contact, high homogeneity, an appointed CVRM-coordinator who has a high degree of centrality, and a consistently identified opinion leader for CVRM.

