### Construction of network characteristics

*Density* represents the proportion of all possible connections in a network that are actually present. *Homogeneity* represents the similarity of persons within clusters. Similarity of persons will be assessed regarding priority given to preventive treatment and CVRM targets, and other individual characteristics. *Centrality* is a measure for the extent to which a network is organized around a single person and can be divided into in- and outdegree centralization. The first specifies information flow from various network members to a single person, the latter whether information flows from a single person to the other network members.

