### Statistical analyses

Response rates for health professionals and patients will be determined. For patients we will compare response rates between the patient group invited by either a single option for participation and the group that will be offered the choice to participate by either a telephone interview or a paper-based test in order to assess which method is most feasible for including them in social network research using *X*^2^ tests.

Reliability of reported social network connections will be investigated by examining the proportion of all possible connections that will be mutually reported present or absent (reciprocity coefficients in non-directed networks). In accordance with guidelines on handling missing values, we will substitute these by values as provided by responses of other individuals. In case of no information on connections, we will indicate no contact by a filling in a zero in the data [41].

For describing social networks of health professionals and patients we will compute network parameters and provide visualization by using graphic displays. Random permutation tests will be used for comparisons of network characteristics.

For testing our hypotheses and further explorative analyses, controlling for potential confounders, we will use multivariate logistic regression models to investigate the effect of social networks characteristics on professional performance of practice nurses and patients’ self-management and health outcomes.

In the analysis of professional performance of practice nurses regression models will include six network characteristics (density, frequency of contact, homogeneity, presence of informal opinion leaders and CVRM-coordinators, and centrality) as predictors of main interest. As control variables we will include trial arm (intervention vs control group), personal characteristics (amongst others education, years of experience in profession), and practice characteristics (practice size, involvement in other projects or organizations).

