In the analyses of self-management and health outcomes in patients, several multivariate logistic regression models will be estimated. For self-management, separate models will be estimated on physical activity, diet, and smoking. For health outcomes, separate models will be estimated on SBP, cholesterol, and risk score. Models will include four network characteristics as predictors: number of alters with favorable health behaviors, who are also connected among each other, number of alters with depressive symptoms, and number of alters who can provide CVRM-related information. The regression models will be controlled for trial arm (intervention vs control group), patient group (high risk or established CVD), and several personal characteristics: age, sex, ethnicity, marital status, SES, patient activation, therapy adherence, and depressive symptoms.

Two approaches will be used to investigate effects of social network characteristics on change in professional performance of practice nurses and self-management and health outcomes of patients after the intervention period at six month follow-up. First, follow-up outcomes measures will be treated as dependent variables. We will estimate similar models as described above and include baseline measures of outcomes of interest as predictors. Second, we will consider change as the difference between the baseline- and follow-up measures of the diverse outcomes of interest. Ordinal logistic regression models will be estimated, with change represented in three categories; a shift from inadequate to adequate outcomes, no change, and shift from adequate to inadequate outcomes.

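### The specified models test the professional-network hypothesis only in part: the coordinator's own centrality is not a predictor, and no specified health-outcome model carries the professional-network predictors

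*Protocol article*

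**What the plan says.** **The hypothesis.** Under Hypotheses on health professionals, the prediction has two outcome limbs: "Patients are more likely to receive recommended CVRM and reach CVRM targets in general practices which have social networks characterized by" followed by a list of features. The last two features are "an appointed CVRM-coordinator who has a high degree of centrality, and a consistently identified opinion leader for CVRM". Theoretical background gives the reasoning at the level of the person: "individuals with high centrality are expected to be present in social networks as CVRM-coordinators or case managers".

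**The measure.** Construction of network characteristics treats centrality as "the extent to which a network is organized around a single person", with separate indegree and outdegree versions of centralization.

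**The performance model.** Statistical analyses assigns six network characteristics to the model for practice nurses' performance. It names density, contact frequency and homogeneity first, and then lists "presence of informal opinion leaders and CVRM-coordinators, and centrality".

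**The patient models.** The same section describes separate models for SBP, cholesterol and risk score, alongside those for self-management. It says: "Models will include four network characteristics as predictors". All four concern the patient's own contacts: those with favourable behaviours, the connections among them, those with depressive symptoms, and those able to give CVRM information.

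**The declared outcomes.** Health care professionals and their alters (within Outcomes & measures) names the effect of network characteristics on both nurses' performance and patients' health outcomes as a main outcome.

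**The concern.** There are two gaps between the hypothesis and the models.

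First, the hypothesis is about where one identified person, the coordinator, sits in the network. The predictor describes the shape of the whole network, and the person at its centre could be a general practitioner, an assistant or anyone else. Coordinator presence enters as a separate term, and no interaction or coordinator-specific position is given. A null or reversed coefficient for centrality would therefore say little about whether a central coordinator helps.

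Second, the limb on reaching targets is announced twice, in the hypothesis and as a main outcome for professionals, but the detailed predictor lists do not carry it out. The six-month models that adjust for baseline are described as similar to the baseline ones, so the gap passes into that analysis of change as well.

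At stake are one hypothesised determinant measured by the wrong quantity and one declared main outcome with no specified analysis.

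**Working it through.** The protocol gives no figure on this point to reproduce. The check compares the sections and then illustrates the first gap with arithmetic.

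**1. Are the coordinator and centrality terms separate?** The plan counts six characteristics. Density, contact frequency and homogeneity make three. The total of six is reached only if opinion-leader presence, coordinator presence and centrality are three further terms (3 + 3 = 6). So centrality is not tied to the coordinator.

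**2. Can the listed terms tell a central coordinator from a peripheral one?** Assume a practice of 10 staff with one named coordinator and a reciprocated star network, in which one hub exchanges information with each of the 9 others. The practice size and shape are my assumptions.

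- Degrees: hub 9, each of the 9 leaves 1. In- and outdegree are equal because ties are reciprocated.
- Density = ties present / ties possible = 18 / (10 × 9) = 0.20.
- In- or outdegree centralization = sum of (maximum degree − own degree) / (n − 1)² = 9 × (9 − 1) / 81 = 72/81 = 0.89. With the undirected denominator (n − 1)(n − 2) = 72 it would be 1.0. The protocol specifies in- and outdegree, so 0.89 is the relevant value.
- Coordinator's normalised degree = own degree / (n − 1): 9/9 = 1.0 if the hub, 1/9 = 0.11 if a leaf.

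| | Coordinator is hub | Coordinator is leaf |
|---|---|---|
| Coordinator present | yes | yes |
| Density | 0.20 | 0.20 |
| Centralization (in or out) | 0.89 | 0.89 |
| Coordinator's own degree | 1.0 | 0.11 |

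With contact frequency, homogeneity and opinion-leader status held equal, all six listed predictors coincide. Only the quantity in the hypothesis differs.

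The measures can also diverge in the other direction. In a fully connected practice everyone has degree 9, so the coordinator's normalised degree is 1.0 while centralization is 0.

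**3. Which predictors meet which outcomes?**

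| Outcome | Six professional-network predictors | Four patient-network predictors |
|---|---|---|
| Nurses' performance | specified | not listed |
| Self-management | not listed | specified |
| SBP, cholesterol, risk score | not listed | specified |

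The hypothesis and the declared main outcome for professionals need an entry in the first column of the last row, and none is given.

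**4. Opinion leader.** The hypothesis asks for consistent identification; the model lists presence. Each professional writes down one influential person, from inside or outside the practice, and no agreement rule is stated. The two wordings differ, but the article does not fix how presence will be coded.

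**The case against.** Much of the hypothesis is tested. Density, contact frequency and homogeneity enter as hypothesised, and receipt of recommended care is modelled through nurses' performance. A reader might infer that the models miss the hypothesis altogether; the protocol does not support that.

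A reader might also infer that reaching targets is left wholly unanalysed. That is too strong. A general sentence in Statistical analyses says that logistic models will relate network characteristics to health outcomes as well as to performance. It does not say whose networks, however, and the explicit lists that follow supply only patient-network predictors for those outcomes. What stands is a mismatch between what is announced and what is specified.

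For opinion leaders, a reader might infer that a single nomination makes the indicator positive, so that it hardly varies between practices. The protocol states no such rule. Presence may be shorthand for the consistency criterion in the hypothesis, and an article may leave the coding to the full plan. This remains a matter of aligning the wording.

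On centrality, the opposition to density is exact only at the extreme of a complete network, and both terms enter the model separately. The coordinator's own degree is not free of density either: the network mean of normalised degree equals density (in the star, 18/90 = 0.20). These points temper the argument but do not put the coordinator's position into the model.

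Finally, the aims and hypotheses are described as exploratory, which limits the weight of the point.

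**Conclusion.** The point holds in part. Two defects stand.

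- **Coordinator centrality.** The hypothesis concerns the coordinator's own position, while the specified predictor is whole-network centralization. In the star example the listed predictors are identical for coordinators whose normalised degrees are 1.0 and 0.11. The conclusion follows from the definitions; the size rests on the assumed 10-person reciprocated star.
- **Reaching targets.** The professional-network effect on patients' health outcomes is declared a main outcome, but none of the three specified health-outcome models (SBP, cholesterol, risk score) contains a professional-network predictor. This rests on the text alone.

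The opinion-leader wording is a minor third item, and nothing in the documents allows its effect to be quantified. Because the study is exploratory, the consequence is a test aimed at the wrong quantity and an announced analysis left unspecified. The sample-size calculation is not affected.

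**What to change.** 1. **Construction of network characteristics and the performance model.** For the coordinator hypothesis, use the normalised in- and outdegree of the named CVRM-coordinator. The questionnaire allows several names, so state a rule, for example the maximum among those named, with practices naming none as a separate category. Keep centralization as a descriptive measure only.
2. **Health-outcome models.** Add models of SBP, cholesterol and, for patients without established CVD, risk score on the professional-network characteristics, accounting for clustering by practice.
3. **Opinion leader (wording).** Code it by agreement among nominations, for example the largest share of respondents naming the same person, to match the hypothesis.

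No new data are needed: the rosters, coordinator names and opinion-leader nominations are in the professionals' questionnaire, and the health outcomes are abstracted from records. The cost is three extra models at baseline, and up to 3 outcomes × (1 baseline + 2 change approaches) = 9 if both change approaches are followed. These predictors vary only between practices, and 30 are planned, so estimates will be imprecise and should be reported as exploratory. The coordinator's degree will also be correlated with density, which should be acknowledged when the two are interpreted together.

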### Sample

The sample will consist of health care professionals, patients with high risk for CVD or established CVD and their alters.

#### **
*Health care professionals*
**

We will include all health care professionals working in general practices participating in the RCT and who are involved in patient care (typically, general practitioners, practice nurses, and practice assistants). Based on power calculations in the RCT, 30 practices are planned to be included.

#### **
*Patients*
**

Eligible patients are adults aged 18 or older, with high risk of CVD or established CVD and who are capable of providing informed consent [30]. Patients with high risk for CVD have a risk score of 20% or higher of 10-years-morbidity and mortality due to CVD. International Classification of Primary care (ICPC) codes will be used to extract eligible patients from medical records. Exclusion criteria are: diabetes mellitus, pregnancy and lactation, terminal illness, cognitive impairments, and poor language skills. Per practice we plan to include 15 patients with established CVD and 15 at high risk.

#### **
*Alters*
**

*Alters of health care professionals* will comprise individuals with whom information on CVRM is exchanged but who are not part of the general practices’ network, as well as opinion leaders from outside general practices. We aim to include all alters of health care professionals.

*Alters of patients* include key individuals for information exchange, which most likely will be spouses or children of patients. We aim to include up to four persons considered to be important for dealing with patients’ condition or disease as indicated by the included patients in our measurements.

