### Health care professionals and their alters

Main outcomes for health professionals will consist of 1) the description of social networks and 2) the hypothesized effects of several social network characteristics, controlled for possibly confounding variables, on professional performance of practice nurses and patients’ health outcomes. Additionally, exploration of effects on social network characteristics on changes in professional performance after completion of the RCT are of main interests.

#### 

**Professional performance** Professional performance reflects application of recommendations for personalized counseling and education of CVRM patients by practice nurses. Professional performance is represented with a dichotomous score, reflecting adequate or inadequate performance. We will consider personalized lifestyle advice as provided by practice nurses to be adequate when at least one of the following conditions is met:

1. There is a record in the patients’ medical file or other healthcare provider-based records that the patient has received advice on at least one lifestyle item as specified in prevailing guidelines of CVRM; diet, smoking or physical exercise, and which has been relevant for the individual patient in the previous six months. At least one target, made up maximally 15 months ago, for improving an aspect of lifestyle should be recorded. Also, practice nurses are required to make a register note when a patient has an adequate lifestyle.

2. There is a notation in the patients’ medical file that the patient has none, mild or major depressive symptoms and that the patient has been referred to E-health, a physical exercise group, or depression treatment respectively.

#### **
*Other measurements on health care professionals will include*
**

##### 

**Descriptive variables** Descriptive measures will include size of practice (number of staff and patients), profession, and involvement in other organizations or projects and will be measured using the Epa Cardio abstraction tool for medical audit instrument [32].

##### 

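### The professional-performance model adjusts for no patient characteristic, although its outcome is scored on each patient's file, so differences in patient mix between practices can be attributed to the network

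*Protocol article*

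**What the plan says.** **Outcome.** Under Health care professionals and their alters, the protocol states: "Professional performance is represented with a dichotomous score, reflecting adequate or inadequate performance". The score is built from individual files. Condition 1 begins: "There is a record in the patients’ medical file or other healthcare provider-based records that the patient has received advice on at least one lifestyle". Such advice counts only if it concerns something "which has been relevant for the individual patient in the previous six months". Condition 2 begins: "There is a notation in the patients’ medical file that the patient has none, mild or major depressive symptoms". It also requires the referral that matches that status. Meeting either condition is enough. The hypotheses on health professionals are also worded in terms of patients receiving recommended care, with the practice's network as the exposure.

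**Adjustment of the performance model.** Statistical analyses names six network characteristics as predictors and then states: "As control variables we will include trial arm (intervention vs control group), personal characteristics (amongst others education, years of experience in profession". Practice size and involvement in other projects or organizations complete the list.

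**Adjustment of the patient models.** The following paragraph controls the self-management and health-outcome models for trial arm, for the patient's activation, adherence and depressive symptoms, and for "patient group (high risk or established CVD), and several personal characteristics: age, sex, ethnicity, marital status, SES".

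**Sampling.** Under Sample: "Per practice we plan to include 15 patients with established CVD and 15 at high risk".

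**The concern.** The exposure is a property of the practice, it is not randomised, and there are 30 practices. The outcome is recorded per patient. Whether advice, a lifestyle target or a referral is on file can depend on the patient as well as on the nurse. In this structure patient mix is an ordinary candidate confounder, and with 30 practices differences in mix cannot be relied on to average out.

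The protocol treats such variables as confounders when the outcome is self-management or blood pressure, but not when the outcome is care recorded for the same patients. The Discussion suggests that network findings could inform how healthcare teams are composed. An association that partly reflects who is registered with the practice would be a poor basis for that, and case mix could equally hide a real association.

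**Working it through.** **1. No figure in the plan applies.** The only sample size calculated for this study, 338 patients, concerns invitation response rates. It reproduces (two-sided, 50% v 65%: 340 with pooled variance, 334 unpooled) and has no bearing here. The document gives no input for the association between patient mix and network, so everything below rests on assumed values.

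**2. The adjustment sets side by side.**

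| Variable | Collected | Performance model | Patient models |
|---|---|---|---|
| Trial arm | yes | yes | yes |
| Professional's education, experience | named as controls | yes | no |
| Practice size, other projects | yes | yes | no |
| Patient group | yes | no | yes |
| Age, sex, ethnicity, marital status, SES | yes | no | yes |
| Patient's educational level | yes | no | no |

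The examples given for personal characteristics in the performance model are the professional's own. The words showing that the list is open attach to those examples and do not point to patients.

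**3. What omission does, to first order.** With no true network effect and one omitted binary patient trait,

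spurious log OR per SD of network score ≈ ln(OR of trait) × ρ × s,

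where ρ is the correlation of practice mix with the network score and s is the between-practice SD of trait prevalence.

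- ρ = 0: the shift is 0 and the OR is 1.00.
- Trait OR 2, ρ = 0.3, s = 0.10: 0.693 × 0.3 × 0.10 = 0.021, OR 1.02.
- Trait OR 3, ρ = 0.5, s = 0.20: 1.099 × 0.5 × 0.20 = 0.110, OR 1.12 (simulation: 1.10).
- Patient group with the 15/15 quota met: s = 0, so the shift is 0 whatever the other values.

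**4. Simulation.** 30 practices × 30 patients, trait prevalence about 40%, no true network effect, logistic regression with practice-clustered standard errors, 400 runs per cell.

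*Set A:* s of 10 to 20 percentage points, trait OR 2 to 3, ρ 0.3 to 0.5, t reference on 28 df. Without the trait: OR 1.02 to 1.10, false positives 5 to 18%. With it: OR 0.99 to 1.01, false positives 4 to 7%.

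*Set B:* between-practice SD on the logit scale, normal reference.

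| Trait OR | SD (logit) | ρ | OR without | False pos. | OR with | False pos. |
|---|---|---|---|---|---|---|
| 2 | 0.5 | 0 | 1.009 | 8.3% | 1.009 | 8.7% |
| 2 | 0.5 | 0.3 | 1.028 | 10.7% | 1.005 | 7.7% |
| 2 | 0.5 | 0.6 | 1.049 | 15.2% | 0.999 | 7.7% |
| 2 | 1.0 | 0 | 0.998 | 7.7% | 0.998 | 7.7% |
| 2 | 1.0 | 0.3 | 1.047 | 11.0% | 1.007 | 6.8% |
| 2 | 1.0 | 0.6 | 1.093 | 29.5% | 1.005 | 6.8% |
| 4 | 0.5 | 0 | 0.994 | 8.0% | 0.994 | 8.5% |
| 4 | 0.5 | 0.3 | 1.052 | 14.5% | 1.004 | 5.8% |
| 4 | 0.5 | 0.6 | 1.098 | 30.2% | 1.002 | 8.0% |
| 4 | 1.0 | 0 | 1.003 | 6.8% | 0.999 | 7.0% |
| 4 | 1.0 | 0.3 | 1.087 | 22.3% | 1.002 | 10.2% |
| 4 | 1.0 | 0.6 | 1.179 | 58.3% | 1.006 | 6.8% |

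In set B the false-positive rate is already 7 to 8% with no confounding. That is the small-cluster error of the sandwich standard error and not part of this point. The Monte Carlo standard error of a rate near 8% is √(0.08 × 0.92 / 400) = 1.4 percentage points.

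**5. Which models are exposed.** The cross-sectional model has no patient term. The first follow-up approach includes the baseline outcome, which takes up part of any stable difference in mix. For the second approach, the three-category change model, no baseline term is described.

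**The case against.** **The article is condensed and a full analysis plan may add covariates.** This would answer the point if the article were silent. It is not: it states a covariate set for each family of models. Nothing excludes patient covariates, and the two lists do not contradict each other, since they serve different outcomes. The point is that the stated set is poorly chosen, not that the text is inconsistent.

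**Sampling two patient groups might be taken as a source of confounding.** A reader might infer this, but the documents point the other way. With 15 and 15 in every practice, patient group cannot differ between practices. It matters only where the quota is missed.

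**The outcome is partly tailored to the patient.** Advice must have been relevant to that patient, an adequate lifestyle is to be noted, and referral follows depressive status. This stands: it reduces dependence on mix, though it does not remove it. The exclusions (for instance diabetes, cognitive impairment, poor language skills) narrow the mix further.

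**A reader might infer that patient mix will be mistaken for a network effect.** The documents do not support that. It needs mix to be associated with the network characteristic after the listed adjustments, and no figure for such an association is given. At zero correlation there is no bias.

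**The size may be small and the aims are exploratory.** Both are fair. The lower end of the range is negligible, and the 58% needs the most adverse cell. This limits the weight of the point, but the remedy is cheap enough to be worth making.

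**Conclusion.** The point holds as a possibility that the plan leaves open without need. A score taken from patient files is modelled against a non-randomised practice-level exposure in 30 practices, and the stated adjustment set contains no patient variable although suitable ones are collected. Differences in age, sex, ethnicity, education or socioeconomic status can therefore be credited to the network, chiefly in the cross-sectional and change-category models.

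The figures illustrate the size; they do not estimate it. The spurious OR per SD of network score runs from about 1.00 with no correlation, through 1.02 to 1.10 at correlations of 0.3 to 0.5, to 1.18 at a correlation of 0.6 with a trait OR of 4 and a logit SD of 1.0. They assume one fully observed binary trait at about 40% prevalence and no other covariates.

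**What to change.** In Statistical analyses, extend the control variables of the professional-performance models to include, at patient level, age, sex, ethnicity, marital status, educational level and SES, with patient group added as a design variable and patients nested in practices. Apply this to the cross-sectional, follow-up and change models.

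The whole patient-model list should not be copied over. Patient activation, therapy adherence and depressive symptoms may themselves be influenced by care, and depressive status forms part of the outcome definition. Covariates that precede care are the safer set.

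The cost is wording only. All these variables are already to be collected, and patient-level terms use none of the limited practice-level degrees of freedom. The small downside is item non-response: the sociodemographic covariates come from the patient questionnaire, whereas performance comes from the file. The plan should state how missing covariates are handled, for example by multiple imputation that respects the practice level, so that scored files are not dropped. Showing patient characteristics by practice, and the network estimates with and without these covariates, would let readers see whether case mix mattered.
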